### Analysis of outcomes

We will use a generalized linear mixed models with logit link to test the hypothesis for the reduction in exacerbation rates specifying the fixed effects of intervention and time and random effects for practice and practice*time. These random effects are based on the statistical model that accounts for separate correlations among individuals in the same cluster at the same or different time points, and random variation in the secular trends across clusters [89]. To control for repeated measures within individuals, we will include a separate random effect for each patient. We will test the effect of implementing Coach McLungs^SM^ with the intervention fixed effect (two-sided, *p* = 0.05) as well as mean difference and corresponding 95% confidence interval for the intervention effect. The study design and models proposed account for the establishment of causal treatment effects at the patient level [109].

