## Background

Asthma is a respiratory disease affecting the lungs which results in significant illness and death regardless of age. In the United States, asthma is one of the top chronic diseases affecting over 6 million children, with 80,000 hospitalizations, 185 deaths, over 500,000 Emergency Department (ED) visits, and more than 7.9 million missed school days every year [1–9]. Significant disparities in asthma outcomes occur by sex, race, ethnicity, and socioeconomic status [10–19]. Pediatric males have a higher prevalence of asthma and are more likely to have inpatient stays for asthma [14, 15, 20, 21]. Minority children are less likely to utilize controller medication [10, 11, 22–27] with African American children having 2 to 3 times higher rates of acute care visits compared with non-Hispanic white children and a 4.9-fold higher asthma death rate [10, 11, 28–31]. Inner cities, such as Charlotte, NC, are epicenters for asthma health disparities in the US, with children 10–17 years old bearing a disproportionate share of the burden [32–35].

Numerous individual- (provider, patient), interpersonal- (family), and system-level (healthcare policies, health systems operations) factors contribute to poor asthma outcomes [22, 36–42]. These documented disparities may persist due to the lack of a comprehensive approach for asthma care that is scalable, sustainable, and widely disseminated [22]. Previous programs, such as asthma action plans [43], allergen remediation [36, 37, 44–46], education [24, 47–49], peer support [50], case management [51–53], or community health workers [54–57], have shown positive results on a local level or in the short-term; however, no single program demonstrated widespread and sustainable outcomes improvement.

Improved asthma outcomes are associated with effective communication strategies between patients and providers [58–60]. Shared decision making (SDM) is a patient-centered process based on a platform of motivational interviewing, in which patients and providers work together to make decisions, select tests, treatments, and jointly create care plans based on evidence that balances risks with patient preferences and values. Previous studies show this SDM intervention is associated with improved outcomes for pediatric and adult patients with asthma [6, 61–67].

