All outcomes and survey data will be collected and provided quarterly to the SAC in order to evaluate the implementation. Barriers and facilitators that emerge from 6-, 12-, and 18- month CFIR post-implementation surveys (see Additional files 3–5) will be reviewed by the SAC and feedback will be provided to the practices at 6-month follow up meetings.

Specific Aim 2: Conduct ongoing evaluation of patient-centered outcomes.

Based on a review of the implementation evaluation literature [61, 86, 87], the RE-AIM framework (Reach, Effectiveness, Adoption, Implementation, Maintenance) will be used for implementation evaluation. Reach, Maintenance: the number of patients and providers utilizing Coach McLungs^SM^ over time at each practice will be measured. As Coach McLungs^SM^ will be accessed through the EMR, we will be able to measure the number of times the intervention is delivered. Effectiveness: Patient health outcomes data of acute care visits for asthma exacerbations will be analyzed for patients who have a diagnosis of asthma (ICD-10 codes J45.0-J45.998) irrespective of intervention, allowing measurement of any outcome improvements over the life of the study. Data will be assessed at 6, 12 and 18 months for patient outcomes.

Specific Aim 3: Dissemination: Disseminate results and strategies for primary care implementation both locally and nationally. We will disseminate through local stakeholders, practice-based research networks, asthma advocacy national organizations, and academic research meetings for healthcare, primary care and asthma. We expect multiple methods, qualitative and quantitative results manuscripts in subsequent years (Fig. 1).

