## Methods

We propose cross-sectional stepped-wedge cluster randomized design with a phased, randomized rollout. Twenty-one practices will be assigned the intervention randomly over the course of 30 months with the first 6 months used as a baseline period (total rollout time period 36 months) [88]. The research team will be blinded to practices that will receive the intervention until 3 months prior to implementation. Randomization is generated by the study statistician using SAS version 9.4, stratified by practice size (Table 1). Once the intervention has been rolled out at the practice, patients will be exposed to Coach McLungs^SM^ as they are seen by providers for their asthma. This implies that crossover to the intervention is not only at the practice level but also potentially the patient level [89]. The patient level exacerbation rates will be measured at 6-, 12-, and 18-month intervals pre- and post- the interaction with Coach McLungs^SM^.

**Table 1 Tab1:** Stepped-Wedge Design for *Coach McLungs*^*SM*^ Implementation with 6-month time intervals for each

	**Baseline (6 mos)**	*Time 1 (6 mos)*	*Time 2 (6 mos)*	*Time 3 (6 mos)*	*Time 4 (6 mos)*	*Time 5 (6 mos)*
Practices 1–4	**120**	*120*	*120*	*120*	*120*	*120*
Practices 5–8	**120**	**120**	*120*	*120*	*120*	*120*
Practices 9–13	**150**	**150**	**150**	*150*	*150*	*150*
Practices 14–17	**120**	**120**	**120**	**120**	*120*	*120*
Practices 18–21	**120**	**120**	**120**	**120**	**120**	*120*

Bold: control period, Italics: intervention period

The aim of implementation is to disseminate Coach McLungs^SM^ to patients most at need in the primary care setting. Often these patients have problems with managing asthma as a chronic disease and adhering to treatment plans. Primary care providers and staff are aware of the need to better prepare patients for chronic asthma management and fully support the Coach McLungs^SM^ SDM intervention.

Inclusion Criteria for this study are: (1) having attained the age of at least 5 years but less than 18 years at enrollment; (2) having established mild, moderate, or severe persistent asthma with a diagnosis verified by practice providers; (3) English or Spanish speaking. 4,981 patients in 21 practices aged 5–17 were seen in primary care for asthma in last 18 months (Table 2).

**Table 2 Tab2:** Number of Primary Care Patients Age 5–17 Diagnosed with Asthma October 2017 to March 2019

	# Eligible patients at proposed 21 practices	# Patients in healthcare system

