### Study design

The stepped-wedge design is useful for the evaluation of complex healthcare interventions [89], particularly when the intervention is believed to be beneficial with minimal risk [104]. This design is increasingly being used to evaluate interventions involving healthcare delivery due to: (1) allowing the research team and clinical teams to rollout the intervention in small number of facilities in a timely, systematic manner [105]; (2) increasing participation and buy-in since all facilities will eventually get to implement the intervention during the study [89, 106, 107]; and (3) increase in statistical power compared to a cluster randomized trial due to increase in data collection and within cluster comparisons [89]. Our intervention is applied at the practice (cluster) level but the exacerbation rates are obtained on patients. In this cross-sectional cohort design, we will include both patients who are present at baseline and new patients coming into the practice throughout the study period. All patients in a practice would be eligible but providers may decide that some patients do not need to utilize Coach McLungs^SM^ [108].

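### The stated primary model has no patient-level baseline covariates, so a case-mix change caused by the switch could enter the intervention effect; the size is conditional and the precision gain small

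*Protocol article*

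**What the plan says.** - **Model.** The protocol article, Analysis of outcomes, specifies a logit mixed model, "specifying the fixed effects of intervention and time and random effects for practice and practice*time". It adds: "To control for repeated measures within individuals, we will include a separate random effect for each patient". No patient-level covariate is named there or elsewhere in the article.
- **Claim made for the model.** The same section states: "The study design and models proposed account for the establishment of causal treatment effects at the patient level".
- **Open population.** Study design says "we will include both patients who are present at baseline and new patients coming into the practice throughout the study period".
- **Who is counted.** Aims and anticipated outcomes takes all patients with an asthma diagnosis code, "irrespective of intervention, allowing measurement of any outcome improvements over the life of the study". The inclusion criteria in Methods require "having established mild, moderate, or severe persistent asthma with a diagnosis verified by practice providers".
- **Prognostic factors.** Background states: "Significant disparities in asthma outcomes occur by sex, race, ethnicity, and socioeconomic status". It puts acute care visits in African American children at 2 to 3 times those in non-Hispanic white children.
- **Data at hand.** Table 2 tabulates sex, race and ethnicity for children aged 5-17. Table 3 lists utilisation at month 0, and Methods measures exacerbations before as well as after use of the tool.

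**The concern.** Randomising the step balances practices over time. It does not randomise the children who join a practice once it has switched. The period effects remove only changes common to all practices, so a change in case mix that follows each practice's own switch stays with the intervention term. The patient random effect compares a child with itself, which helps only for children seen on both sides of the switch.

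The article makes a switch-linked change plausible. Practice providers verify the diagnosis and know when their practice has switched. The kick-off that marks the switch includes a refresher on asthma guidelines (Table 4). If training leads providers to recognise and code milder asthma, the post-switch group is lower risk and the tool looks better than it is. If higher-risk children are drawn in, a real benefit is hidden. Baseline covariates would also remove some prognostic variance from the error term.

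**Working it through.** **1. The plan's own power figure.** This sets the precision baseline. Inputs from Sample size justification: 21 practices, 6 periods, switches of 4/4/5/4/4, 30 patients per practice-period, ICC ρ = 0.20, cluster autocorrelation π = 0.9, individual autocorrelation τ = 0.5, 40% versus 30%, two-sided 0.05. For variance v, the covariance of one practice's six period means is

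V = ρv[πJ + (1−π)I] + (1−ρ)(v/30)[τJ + (1−τ)I].

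The intervention variance comes from generalised least squares with six period effects, and power = Φ(0.10/SE − 1.96).

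- τ = 0 (new children each period), v = 0.24: SE 0.0335, power 84.8%. With v = 0.25, power is 83.3%. Both are close to the stated 84%.
- τ = 0.5 as printed: SE 0.0284 and power 94.0% with v = 0.24. Across the variance choices tried, power is 92-96%.

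The stated 84% is therefore matched only without repeated patients. That is a separate matter and does not affect this point.

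**2. Precision from covariates.** The R² is assumed; the document gives none. Covariates explaining a share R² of individual-level variance reduce (1−ρ)v by that share, taken from the patient component when patients repeat.

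| Case | R² | Variance ratio | Power |
|---|---|---|---|
| New children, 30 per cell, v = 0.24 | 0 | 1.000 | 84.8% |
| same | 5% | 0.972 | 85.8% |
| same | 10% | 0.944 | 86.7% |
| same | 20% | 0.888 | 88.7% |
| New children, 100 per cell | 10% | 0.972 | – |
| Same children followed, τ = 0.5, 30 per cell | 10% | 1.000 | no change |
| same | 20% | 0.9995 | no change |

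At R² = 10% the gain is 3-6% of variance with new children and none with followed children.

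**3. Bias if the switch changes who joins.** Assumed: the high-risk share among children joining after the switch is 10 points lower, and high-risk children have 20 points more exacerbation risk.

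- Full turnover: 0.10 × 0.20 = 2.0 points.
- Partial turnover, from a linear-model simulation including the patient random effect. The bias is the estimate with the shift minus the estimate without it:

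| Turnover per period | Without covariate | With covariate |
|---|---|---|
| 25% | 0.0013 − 0.0034 = −0.2 points | 0.0035 − 0.0035 = 0.0 |
| 50% | −0.0081 + 0.0019 = −0.6 points | −0.0017 + 0.0016 = 0.0 |
| 100% | −0.0254 + 0.0049 = −2.0 points | −0.0055 + 0.0057 = 0.0 |

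Against the 10-point planning effect this is 2% to 20% (0.2/10 to 2.0/10). Against the 5-point forecast in Anticipated outcomes (40% to 35%) it is 4% to 40%. At full turnover, shifts of 5-20 points and risk differences of 10-30 points give 0.5 to 6 points.

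**4. A practice-wide illustration from Table 2.** African American share: 1995/4981 = 0.40. With an overall rate of 0.40 and risk ratio RR, the risk in other children is p0 = 0.40/(0.60 + 0.40·RR). A 5-point change in share moves the rate by 0.05·p0·(RR − 1): 0.83, 1.43 and 2.22 points for RR 1.5, 2 and 3. Both the 5-point change and the use of these ratios for the composite are assumptions. The 2-3 fold figure is for acute care visits, whereas the composite is mostly oral steroids (35%, against 10% with ED visits). If joiners are 25% of a period's patients, they would have to differ by 5/0.25 = 20 points to move the practice by 5.

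**5. Completeness of the fields.** Unknown ethnicity: 588/4981 = 11.8%. Other/unknown race: 622/4981 = 12.5%.

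**The case against.** The strongest objection is that the model is a valid stepped-wedge analysis as it stands. Step timing is randomised, so case mix is balanced in expectation. Period effects remove shared trends, and chance drift within a practice is noise, not bias. All diagnosed children are analysed whether or not they used the tool, so selection on tool use is excluded. A covariate list is often left to the analysis plan, which is not shown. All of this stands.

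A reader might infer that case-mix change will bias the result, or that the model is wrong. The documents do not support that: bias needs a switch that systematically changes who is diagnosed or seen, and nothing in the article shows that it will. Nor may one infer that the covariates are complete for every child; about 12% are unknown or in a mixed category.

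The remedy also has limits. It corrects only for measured factors. A child who joins after the switch is the one most likely to have no earlier record, so prior exacerbation says least where it is needed most. A change in diagnostic threshold may not show in age, sex or race.

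What remains is that the article states the model's terms and makes a patient-level causal claim for it. Analysing everyone diagnosed does not prevent selection into the diagnosed group.

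**Conclusion.** The point holds as a conditional weakness and a reasonable improvement, not as a demonstrated error. The stated model leaves the intervention effect open to a switch-linked change in measured case mix among children seen on only one side of the switch. Under the assumed shift of 10 points and risk difference of 20 points, the bias runs from about 0.2 points at 25% turnover to 2.0 points at full turnover. It can favour the tool or count against it. The precision argument is secondary: the gain is nil if the same children are followed and about 3-6% of variance if they are new each period. The turnover, the shift, the risk difference and the R² are all assumptions; the documents give none of them.

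**What to change.** Pre-specify fixed effects for:

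- age;
- sex;
- race and ethnicity in the Table 2 categories, keeping an unknown level;
- any exacerbation in a fixed look-back (for example 12 months), with a level for no earlier record.

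Measure all of them before the child's first study period, so that recoding after training cannot change the covariates. Because a logit model's conditional odds ratio changes when covariates are added, average the fitted model over the patients and report the standardised risk difference with its confidence interval. Show the unadjusted model as a sensitivity analysis. If an analysis plan already lists covariates, align the two documents.

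The cost is a sentence or two in the analysis section, a few fields from an extract already planned, and a little extra analysis. No new data collection is needed where the look-back history is in the record. The drawbacks are the unknown categories and the fact that only measured shifts are addressed.

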Aged 5–17	4981	14,283
Male	2985	8528
Female	1996	5755
African American	1995	4863
Caucasian	2364	7147
Other/Unknown	622	2273
Hispanic/Latino	313	1141
Non-Hispanic Latino	4080	10,784
Unknown Ethnicity	588	2358

Providers and clinic staff will offer Coach McLungs^SM^ to all patients and those deemed in need of extra asthma education. To simplify the selection process, practices may choose to offer Coach McLungs^SM^ to all patients with asthma, regardless of asthma severity. An additional enrollment table will track providers who are using Coach McLungs^SM^ at the participating practices. Patient-centered outcomes will be monitored from available EMR data throughout the course of the study by the research team. End-users will be primary care patients, providers, and staff. The types of patients will be primary care pediatric patients and their caregivers (most likely parents) with asthma, aged 5–17 (Table 2).

A key feature of our implementation approach will be the use of iterative process improvement cycles (Fig. 2) to implement this process which will be monitored by the SAC, to evaluate both the process and outcomes of the intervention.

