**Fig. 2 Fig2:**
[figure not shown]
Process improvement

Multiple patients, primary care providers, and staff engaged with the SAC through development of this virtual SDM intervention, a previous pilot study, and planning for this current implementation study in primary care are involved in process improvement. We plan to use an iterative quality improvement method, where the implementation will be adjusted at each practice based on feedback from the SAC after advisory members are updated with ongoing outcomes and survey results.

Domains from the CFIR [90–94], such as inner setting (structural characteristics, culture, networks and communications, and tension for change) and outer setting (patient needs and resources, external policies, and incentives), will be incorporated into the implementation evaluation surveys (see Additional files 1, 3–5) [95–97]. The RE-AIM framework represents a flexible, comprehensive model according to which we will execute and evaluate the SDM implementation (Fig. 3). Adapting RE-AIM elements allows for full evaluation of the intervention at different time points during the study [98, 99].

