Anticipated barriers to Reach are based on our prior implementation knowledge of the need for practices to have flexibility in their approach to implementation. By using a tailored approach [99], we anticipate to fully and effectively implement Coach McLungs^SM^ at all 21 practices. We will (1) use a flexible approach with practices that includes a 6-month step time window in order to mitigate circumstantial barriers such as practice availability for kick-off; (2) address staff and provider preferences for each practice, such as who is needed at meetings, does the practice want a staggered or practice-wide approach to implementation; (3) the practice may request extra support for items such as extra training for communication skills (usually motivational interviewing or shared decision making), use of asthma guidelines, asthma medication management education; (4) practices may request support in considering how to adapt flow and timing of patient visits in order to maximize use of Coach McLungs^SM^. The implementation training will be adapted from the ERIC (Table 4).

**Table 4 Tab4:** Implementation plan based on expert recommendations for implementing change (ERIC)

ERIC element	Element description for *Coach McLungs*^*SM*^ implementation
Use data experts	Director of data analytics will lead team to acquire, manage, and report data generated by implementation effort
Provide local technical assistance	Practice rollouts will be conducted by the lead research team with the implementation team providing technical assistance
Audit and provide feedback	Develop individual primary care practice feedback summaries including CFIR results and combined performance at other implementation and control sites and report out to practices at 6- 12- and 18- months post-implementation based on their preferences which include but no limited to: email, webinars, lunch-and-learn meetings and Skype conference calls
Use an implementation advisor	An implementation team will advise on the use of implementation frameworks and evaluation plan
Implementation facilitation	The lead reach team are both experienced practice facilitators with both *Coach McLungs*^*SM*^ and the previous paper-based asthma SDM toolkit

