### Sample size justification

We used a method to estimate sample size that takes into account the cluster randomization and the stepped-wedge design [88]. Our study design includes 21 clusters (facilities) with 6 time periods (including the baseline), 5 steps, 4 facilities switching from control to intervention at each step (except the third step will have 5), and an average of 30 patients per practice being continuously followed. Thirty patients is conservative as the typical number in a 6-month period is approximately 100. We conducted sample size analyses accounting for intracluster correlation (ρ = 0.20), individual autocorrelation (τ = 0.5), and cluster autocorrelation (π = 0.9) [88]. This design achieves 84% power to detect the hypothesized effect size difference of 10% in overall exacerbation between control (40%) and intervention (30%) periods (two-sided, α = 0.05). An effect size of 0.1 translates to a difference between groups of 10% absolute difference between intervention and control overall exacerbation rates.

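### If the intervention effect differs between practices, the primary model's single common effect understates the standard error, so the test and 95% interval become mildly too liberal

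*Protocol article*

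**What the plan says.** **Model.** In the protocol article, Analysis of outcomes describes a generalized linear mixed model with logit link "specifying the fixed effects of intervention and time and random effects for practice and practice*time". For repeated measures it adds: "we will include a separate random effect for each patient". The random effects are justified by correlation within and between time points and by "random variation in the secular trends across clusters". The hypothesis is tested on the single intervention coefficient, two-sided at 0.05, and a mean difference with a 95% confidence interval is promised. No term lets the intervention effect differ by practice, and no reference distribution is named.

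**Delivery.** Several places make delivery a local matter:
- Methods, text after Fig. 2, describes a quality-improvement method "where the implementation will be adjusted at each practice based on feedback from the SAC".
- The paragraph before Table 4 lists preferences to be met at each practice, among them "does the practice want a staggered or practice-wide approach to implementation". It also allows extra training and workflow support on request.
- Methods, text after Table 2: "To simplify the selection process, practices may choose to offer Coach McLungs" to every patient with asthma, whatever the severity.
- Study design lets providers judge that some patients do not need the tool.

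**Power.** Sample size justification states: "This design achieves 84% power to detect the hypothesized effect size difference of 10% in overall exacerbation" (40% against 30%). The inputs are 21 practices, 6 periods, 30 patients per practice, intracluster correlation 0.20, individual autocorrelation 0.5 and cluster autocorrelation 0.9. Variation of the effect between practices is not among them.

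**The concern.** Local choices about who is offered the tool, how it is started and how much training accompanies it tend to persist after a practice crosses over. If they change how well the tool works, each practice has its own effect, and the 21 practices are a sample of such effects. The uncertainty of the average effect then contains a between-practice component that does not shrink as more patients are added. A practice*time effect that is independent from period to period (my reading, since the article does not give its structure) can absorb only part of a shift that lasts through all of a practice's intervention periods.

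The only hypothesis test described, its confidence interval and the stated power all rest on this model, so any shortfall in the standard error reaches the main conclusion.

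**Working it through.** **1. The plan's own power figure.** With total variance s² = 0.35 × 0.65 = 0.2275 and m = 30, the practice-period means have
- a shared practice component: 0.2275 × (0.20 × 0.9 + 0.80 × 0.5/30) = 0.0440
- a period-specific component: 0.2275 × (0.20 × 0.1 + 0.80 × 0.5/30) = 0.00758

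Generalized least squares with fixed period effects and the 4/4/5/4/4 allocation gives SE 0.0277. Power is Φ(0.10/0.0277 − 1.96) = Φ(1.65), about 95%, not 84%. A figure near 84% appears only if the individual autocorrelation is set to 0 (84.8% with s² = 0.24, 83.3% with s² = 0.25). That mismatch is a separate matter. It matters here only because the power lines in step 5 need a stated base.

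**2. What between-practice variation adds.** Let practice effects have standard deviation SD around the average. Roughly SD²/21 is added to the variance of the estimated average. Starting from the simulated SE of 0.0274 at SD 0:
- SD 5 points: √(0.0274² + 0.05²/21) = 0.0295
- SD 10 points: √(0.0274² + 0.10²/21) = 0.0350

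Simulation gives 0.0299 and 0.0354.

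**3. What the planned model reports.** Simulated practice-period means were fitted by REML with random practice and practice*time, using all stated inputs, m = 30, zero average effect and 20,000 runs. The SDs are assumptions.

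| SD (points) | true SE | model SE | ratio | size, z | size, t(19) |
|---|---|---|---|---|---|
| 0 | 0.0274 | 0.0276 | 1.01 | 5.1% | 3.8% |
| 2 | 0.0280 | 0.0278 | 0.99 | 5.3% | 3.8% |
| 3 | 0.0282 | 0.0280 | 0.99 | 5.5% | 4.1% |
| 5 | 0.0299 | 0.0287 | 0.96 | 6.4% | 4.8% |
| 7.5 | 0.0323 | 0.0299 | 0.92 | 7.4% | 5.7% |
| 10 | 0.0354 | 0.0315 | 0.89 | 8.6% | 6.7% |

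Repeat runs gave 6.0% to 6.2% at SD 5 and 8.2% to 8.3% at SD 10 for the z-test. As a hand check, a ratio of 0.89 gives 2 × [1 − Φ(1.96 × 0.89)], about 8%. At SD 10 the model variance rises by 0.0315² − 0.0276² = 0.00023, against a true rise of 0.0354² − 0.0274² = 0.00050. The practice*time term thus absorbs a little under half.

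**4. Other settings (z-test).**
- 100 patients, intracluster correlation 0.20: 6.6% to 7.0% at SD 5 and 9.0% at SD 10.
- 100 patients, intracluster correlation 0.05 (assumed): 8.2% to 9.1% at SD 5 and 12.9% at SD 10. With t(19) it is still 7.1% and 10.2%.

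**5. Remedies.**
- A practice-clustered variance with small-sample correction and t(19) held size between 4.6% and 5.9% in every setting tried.
- At m = 30, a random practice-by-intervention effect gave 4.8% to 5.6% with a z-test over SD 0 to 10. With t(19) it was conservative, at 3.4% to 4.0%.
- Power of the random-effect model for 10 points, z-test, all stated inputs: 94.7% at SD 0, 92.0% at SD 5, 80.8% at SD 10. With t(19): 93.1%, 89.8%, 77.4%.
- From a base near the stated 84% (individual autocorrelation 0), z-test: 85.5%, 82.5%, 71.5%.

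All simulations are linear approximations, on the risk-difference scale, to the logit model.

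**The case against.** **An inert tool cannot have differing effects.** A reader might infer from the tailoring alone that the standard error is too small and that the 5% test exceeds 5%. The documents do not support that. If the tool does nothing anywhere, tailoring creates no variation and the size is 5.1%. Excess false positives need effects that differ yet average zero, so some practices would be harmed. Varying uptake mainly scales an effect and does not reverse it. This stands for the test. It does not rescue the interval: in the linear approximation coverage does not depend on the average effect, so with a real average benefit the nominal 95% interval covers about 94% at SD 5 and 91% to 92% at SD 10.

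**The larger SDs are hard to credit.** With a 10-point average benefit, SD 10 means Φ(−1) = 16% of practices are harmed. With the 5-point benefit in Anticipated outcomes (40% to 35%) it means Φ(−0.5) = 31%. Suppose instead that a 10-point effect at the article's 70% adoption scales with uptake, and that uptake varies between practices by 20 percentage points (an assumption). The SD is then 10/0.70 × 0.20, about 3 points, and the size is 5.5%. This is a fair reason to call the problem modest.

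**The reference distribution is open.** A t(19) reference alone keeps size near 5% up to about SD 5 to 7.5 at 30 per practice-period. That also stands, but the article does not name it, and it is not enough at 100 patients with an intracluster correlation of 0.05.

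**This is material for the analysis plan.** Degrees of freedom often are. But the article itself lists the model's fixed and random effects, so the common effect is a stated choice.

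**Conclusion.** The point holds conditionally. The primary model fixes one intervention effect for 21 practices whose delivery the plan allows to differ. If true effects differ, the standard error for the average effect is too small, the interval under-covers, and the test of zero average effect can exceed 5%.

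At the plan's inputs and 30 per practice-period, the shortfall in the standard error is about 3% to 4% at SD 5 points and about 11% at SD 10. It grows with 100 patients per period, which the article calls typical, and with a lower intracluster correlation.

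These sizes rest on an SD that the documents do not give, on a practice*time effect that is independent between periods, on a z reference, and on a linear approximation. A reader might also infer that the power is badly eroded. With all stated inputs it is still 92.0% at SD 5 (random-effect model, z-test), and drops to 80.8%, below the stated 84%, at SD 10. The change is a worthwhile, inexpensive improvement and does not imply that the planned test is invalid.

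**What to change.** **Analysis of outcomes.** Base the primary test and 95% interval on a practice-clustered variance with small-sample correction and a t reference on practice-level degrees of freedom (21 − 2 = 19). Alternatively, add a random practice-by-intervention effect to the model with those degrees of freedom. Name one as primary and the other as the sensitivity analysis. The clustered variance kept size closest to 5% when paired with t(19).

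**Sample size justification.** Add a short power range over an assumed between-practice effect SD, for example 0, 5 and 10 points. Compute it with all stated inputs, including the individual autocorrelation of 0.5.

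**Cost.** A few sentences, a slightly wider interval and a few points of power. With the random-effect model and all stated inputs, moving from z to t(19) lowers power from 94.7% to 93.1% at SD 0 and from 92.0% to 89.8% at SD 5. No change to the design, the data collected or the rollout is needed.
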